**Fig. 2 f0010:**
[figure not shown]
Schedule of enrolment, interventions, and assessments. Note. T1 and T2 are 2 months and 8 months after baseline respectively. Use of medication and treatment is additionally assessed between T1 and T2; at 4 months and 6 months.

Subsequently, patients commence with the T0 assessment, which contains all outcome measures and an online baseline survey. All outcome assessments are repeated at T1 (2 months after T0, after either iCBT-I and ideally before STEPPS starts, or waitlist) and T2 (8 months after T0, after STEPPS). Use of psychotropic medication and psychotherapeutic treatment is additionally assessed at 4 and 6 months after T0. After T0, patients are randomly assigned to iCBT-I group or the sleep diary-keeping control group. During all phases of the trial, there is one central contact person to provide support to all patients. After completion of the trial, patients in the control condition will be offered identical treatment of remaining sleep problems.

Patients may withdraw from participation at any time, for any reason, without consequences for their awaited treatment. We aim to perform intention-to-treat analyses, so patients that decide to withdraw from treatment are asked to continue the outcome assessments. We will continue recruitment until the intended sample size is achieved or until funding restrictions compel us to end assessments. Data of patients that withdraw from participating are used and reported, unless patients ask us to destroy any data.

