#### Primary outcome measure

2.5.1

The primary outcome is BPD severity, as assessed with the BPDSI-5-4wk. This clinician-rated, semi-structured interview is administered at T0, T1, and T2. The BPDSI-5-4wk is an adjusted version of the BPDSI-5 and measures BPD symptom severity over a period of the past 4 weeks instead of 3 months (Arntz and Wibbelink, 2019). The BPDSI-5-4wk is based on the DSM-5 criteria for BPD and consists of 70 items assessing behaviors and cognitions related to abandonment, relationships, self-image, impulsivity, (para)suicidal behavior, mood swings, feelings of emptiness, anger attacks, and dissociation and paranoid ideation on an 8-point scale ranging from 0 to 10. Scoring options of the BPDSI-5 are adjusted for the BPDSI-5-4wk to (0) never/4 weeks, (3) once/4 weeks, (5) twice/4 weeks, (6) three times/4 weeks, (7) once a week, (8) multiple times a week, but less than half of the week, (9) more than half of the week, and (10) daily. Note that scores 1, 2, and 4 have been omitted, to obtain the same frequency to time ratio used in the BPDSI-5. The BPDSI has high interrater reliability, acceptable to high internal consistencies, and very good discriminant and concurrent validity (Giesen-Bloo et al., 2010).

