#### Adverse effects

2.5.4

Potential adverse effects are assessed in two ways, in line with procedures in van der Zweerde et al. (2016). First by assessment of BPD and insomnia severity. Exacerbation of BPD or insomnia severity from pre- to post-iCBT-I may indicate adverse effects. Second, patients report at T1 and T2 whether they experienced (1) falling accidents, (2) traffic accidents, and (3) any other negative events they think are related to sleepiness or fatigue.

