The study also has some potential limitations. First, there is the risk of drop-out. The trial's thorough assessments may present a significant burden for patients with BPD (traits) that already suffer from severe emotional and behavioral symptoms and sleep problems. Especially patients in the control condition may be prone to drop out, as between T0 and T1, they are not actively engaged in a therapeutic process. We aim to reduce the risk of drop out by submitting patients in the control group to a somewhat active control condition by keeping a daily sleep diary. To prevent too much of a therapeutic effect, no feedback will be given, which in itself entails the risk of patients experiencing the sleep diary as too burdensome. Patients in the iCBT-I condition may experience sleep restriction as burdensome due to the possible temporary increase in emotional symptoms resulting from a lack of sleep. In both groups we aim to minimize drop-out by offering a central contact person to support them throughout the trial. Additionally, patients assigned to the control condition will be offered identical treatment of remaining sleep problems after T2. A second limitation is that a sleep diary-keeping waitlist control condition results in less attention from a professional compared to the iCBT-I condition (although our control condition is more active than a pure waitlist condition). This represents a non-specific, treatment-independent factor that may hinder interpretation of the findings. Finally, we base our power calculation on a meta-analysis of studies investigating the (added) effect of iCBT-I in patients with insomnia and other comorbid psychiatric disorders than BPD (e.g. MDD and PTSD) (Wu et al., 2015). Although BPD represents an archetypical emotion dysregulation disorder, which hypothetically would benefit profoundly from improving (the emotion regulatory function of) healthy sleep, the estimate of the effect size remains indirect, since no studies of iCBT-I in BPD exist.

To conclude, iCBT-I as add-on treatment for patients suffering from both BPD and sleep problems may be a promising way to alleviate BPD symptom severity directly and through improved internalization of subsequent standard BPD treatment.

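### The adverse-effect rule names no control comparison, its open event item depends on the patient blaming fatigue, and the T1 BPDSI window misses the first weeks of sleep restriction

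*Protocol article*

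**What the plan says.** Section 2.5.4 (Adverse effects) gives two routes. The first uses the severity measures: "Exacerbation of BPD or insomnia severity from pre- to post-iCBT-I may indicate adverse effects". No comparison group and no amount of worsening are named. The second is self-report: "patients report at T1 and T2 whether they experienced (1) falling accidents, (2) traffic accidents", and also "any other negative events they think are related to sleepiness or fatigue".

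Other sections determine what these routes can see:

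- Section 2.5.1: the BPDSI-5-4wk, a clinician-rated "semi-structured interview is administered at T0, T1, and T2", "measures BPD symptom severity over a period of the past 4 weeks instead of 3 months". Its domains include "impulsivity, (para)suicidal behavior, mood swings, feelings of emptiness, anger attacks".
- Note to Fig. 2: "T1 and T2 are 2 months and 8 months after baseline respectively".
- Section 2.3.1: sleep restriction enters in the second of five sessions, in a course of 5 to 8 weeks.
- Section 3.1: under sleep restriction the authors foresee a "possible temporary increase in emotional symptoms resulting from a lack of sleep".
- Section 2.5.2.3: diaries kept between T0 and T1 are ruled out as an outcome.
- Sections 2.4 and 2.8: all outcomes are repeated at T1 in both arms and analysed through time-by-allocation terms.

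**The concern.** The article names the harm it thinks most likely, a passing rise in emotional symptoms while sleep is restricted. The harm measures it then describes fit that risk poorly in three ways.

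1. The severity rule is a change across iCBT-I. Only the treated arm has such a change before T1, and BPD severity fluctuates without any intervention. Without the controls' change over the same weeks, a worsened patient cannot be told from ordinary fluctuation.
2. The T1 interview looks back 4 weeks from a visit at 2 months, so a rise early in sleep restriction that has settled by then is not scored.
3. Sections 1.1 and 3 treat self-harm as part of the disorder and link it to poor sleep. Yet the open event item asks for it only when the patient sees tiredness as the cause.

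At stake is the credibility of the harm report, in either direction: harm could be missed because it fell outside the window, or ordinary fluctuation could be read as harm. The authors hope to see the intervention enter clinical guidelines, so readers will want a controlled statement of harm.

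**Working it through.** **The plan's own figure.** The point disputes no figure, but it borrows d = 0.5 and correlation 0.5 from Section 2.7, so that calculation is reproduced first. With two follow-up measurements averaged, n per arm = 2 × ((1.960 + 0.842)/0.5)² × (1 + 0.5)/2 = 62.79 × 0.75 = 47.09, which rounds up to 48 as stated (two-sided).

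**BPDSI window at T1.** Two months is 8 weeks on a loose reading and 365.25/12 × 2/7 = 8.7 weeks by the calendar. Subtracting the 4-week recall, the window opens at week 4.0 or 4.7.

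**Start of sleep restriction.** The article gives no date for session 2. Assume five evenly spaced sessions starting at T0. Session 2 then falls at 5/5 = week 1.0 in a 5-week course and at 8/5 = week 1.6 in an 8-week course.

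| T1 at | Course | Weeks of sleep restriction before the window | Weeks from session 2 to course end |
|---|---|---|---|
| 8.0 weeks | 5 weeks | 4.0 − 1.0 = 3.0 | 4.0 |
| 8.0 weeks | 8 weeks | 4.0 − 1.6 = 2.4 | 6.4 |
| 8.7 weeks | 5 weeks | 4.7 − 1.0 = 3.7 | 4.0 |
| 8.7 weeks | 8 weeks | 4.7 − 1.6 = 3.1 | 6.4 |

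The range is 2.4 to 3.7 weeks. Randomization follows the T0 assessments, which include a one-week diary and four EEG nights. If the 2 months run from the start of T0 and the course begins one week later (an assumption), each figure falls by 1, giving 1.4 to 2.7 weeks.

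**Share of follow-up in which the BPDSI rates self-harm.** T2 at 8 months is 365.25/12 × 8/7 = 34.8 weeks. Two 4-week windows cover 8/34.8 = 23%. Between T1 and the opening of the T2 window, 34.8 − 8.7 − 4 = 22.1 weeks are not covered.

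**Why a one-arm count of worsening cannot be read.** This is illustrative, because the article states no per-patient rule. Assume normal scores with equal SD at T0 and T1, and correlation 0.5. The SD of change is √(2 × (1 − 0.5)) = 1 SD of the score. P(worse) = Φ(−mean improvement / SD of change):

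- Mean improvement 0.5 SD: Φ(−0.5) = 0.31, about 15 of 48 patients.
- Mean improvement 0: Φ(0) = 0.50, or 24 of 48.
- With correlation 0.7 (assumed) and improvement 0.5 SD: Φ(−0.5/0.775) = 0.26.

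A threshold alone does not solve this. If worsening meant at least 0.5 SD, at correlation 0.5 the shares would be Φ(−1.0) = 16% with a mean improvement of 0.5 SD and Φ(−0.5) = 31% with none. The change SD mixes measurement error with real individual change, so these shares are not pure noise. Only the concurrent control arm shows how much worsening to expect without iCBT-I.

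**The case against.** A reader might infer that self-harm not blamed on tiredness goes unmeasured. The documents do not support that. The BPDSI rates (para)suicidal behavior at all three assessments, through a blinded interviewer, with no condition of attribution. The ultra-short BPD-C adds an item for each diagnostic criterion. What remains is coverage: the BPDSI reaches back only 4 weeks each time.

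A reader might also infer that the trial has no controlled data on worsening. It has. BPDSI and ISI are taken in both arms, and the model in Section 2.8 gives a randomised contrast of means at T1. Section 2.5.4 does not forbid a comparison, and its event questions go to patients in general. This stands. But a contrast of means does not show how many patients worsen, and the harm rule as worded does not call on the control arm.

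Nor can it be said that no severity measure sees the early weeks. The 4-week limit is stated for the BPDSI only. The article gives no recall period for the ISI, the BPD-C or the event questions. Early trouble may also surface in the feedback after each session, the video calls or the diary mood ratings. None of these is named as a harm measure, and the treatment-period diaries are excluded as an outcome.

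The length of the gap depends on when iCBT-I starts, which the article does not fix. The 31% and 50% rest on a per-patient count of any increase that the protocol does not state. Both objections stand, so the figures are given as a range and as an illustration.

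Finally, serious adverse event reporting and reliable-change thresholds may sit in the full protocol or an analysis plan, neither of which is shown. Their absence from the article is not part of this point.

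**Conclusion.** The point holds in a limited form. As described in Section 2.5.4, harm is judged by a change across iCBT-I without reference to the controls, and by an open item that filters events through the patient's own attribution. The BPDSI records self-harm regardless of cause for about 8 of 35 weeks. Outside those windows, and leaving aside the BPD-C with its unstated recall period, the described measures catch it only if the patient links it to fatigue. Roughly the first 2.4 to 3.7 weeks of sleep restriction precede the T1 BPDSI window, given evenly spaced sessions starting promptly after T0, and less with a later start. This is the treatment element from which Section 3.1 expects a temporary rise.

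The 31% to 50% range shows why a one-arm count would be uninterpretable. It is not a prediction of what the trial will report. The primary analysis and the sample size are unaffected, and no claim is made that serious adverse event reporting is missing. This is an inexpensive improvement to how harm is measured and reported.

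**What to change.** In Section 2.5.4:

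(a) Report worsening from T0 to T1 on the BPDSI and the ISI in both arms, using a reliable-change threshold set in advance, as a between-arm difference. The data are already collected.

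(b) Have the T1 and T2 event items, in both arms, cover the whole period since the last assessment. Ask about self-harm, suicide attempt, crisis contact or admission, with dates and irrespective of presumed cause. The dates would place events within the early sleep-restriction weeks that the T1 BPDSI cannot reach.

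(c) Report the BPDSI (para)suicidal subscale by arm as a safety outcome.

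The cost is a few items in existing questionnaires, a small ethics notification and one table. No visit is added and the sample size does not change. Patients assessed before the change will lack the new items, so (b) should be reported with its own denominator; (a) and (c) use all patients. The added items record discrete events, so a transient rise in symptoms without an event would still be missed before the T1 window, and the report should say so.

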#### Treatment evaluation

2.5.5

Patients in the intervention condition are asked to evaluate the iCBT-I treatment and its guidance at T1 and T2 (see Supplementary material).

### Randomization

2.6

To guarantee blindness during baseline diagnostic interviews, patients are randomized only after T0 assessments, by an independent researcher. Simple randomization is applied for the first 10 patients. To ascertain balanced, equally sized groups, subsequent patients are assigned using covariate adaptive randomization (group size, sex, age, use of psychotropic medication (current/past/never), time of year of inclusion (week number), baseline severity of BPD (BPDSI and BPD-C scores), insomnia (ISI scores), depression and anxiety (RMT-20 scores), duration of STEPPS (10 or 20 weeks), and diagnosis (BPD or other PD with ≥4 BPD traits)) scripted in R and carried out by an independent researcher. Covariate adaptive randomization is a minimization randomization method which minimizes imbalance on selected factors (covariates) and is in line with the CONSORT statement, which describes this method as equivalent to general randomization (Schulz et al., 2010). Due to the nature of the intervention, the therapist is not blind to treatment condition. The primary outcome measurement (BPDSI) is administered by a blinded and trained researcher. In addition, EEG data is scored by a trained researcher who is blind to experimental condition. All other outcome assessments involve self-report questionnaires that remain blinded. For analysis, all data is re-coded regarding participant number and condition to ensure blinding.

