### Study design

2.1

We will perform a two-armed RCT. In the experimental arm, patients will receive guided iCBT-I for 5–8 weeks followed by a standard BPD treatment (Systems Training for Emotional Predictability and Problem Solving, STEPPS) (Blum et al., 2008). In the control arm, patients are on the waitlist and keep a sleep diary for 6 weeks, followed by STEPPS. The outcomes will be assessed by clinical interviews, questionnaires, sleep diary and EEG headband at baseline (T0), after iCBT-I/waitlist (T1 at 2 months), and after STEPPS (T2 at 8 months). The study design was approved by the Medical Ethics Committee of the VU Medical Centre (METC VUmc; NL76232.029.20). The trial is registered with the Netherlands Trial Register (NL9776).

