#### iCBT-I

2.3.1

The guided, internet-delivered CBT-I intervention i-Sleep was developed and later updated by VU Amsterdam (van Straten et al., 2013; van der Zweerde et al., 2016). It consists of five sessions: (1) Psycho-education on sleep, disordered sleep and sleep hygiene (i.e. guidelines about health and environmental factors influencing sleep), (2) stimulus control training (i.e. use the bed for sleep only to reinforce association of bed with sleeping) and sleep restriction therapy (i.e. restrict time in bed to average time slept), (3) relaxation techniques and minimizing worrying, (4) tackling dysfunctional cognitions about sleep, and (5) summary and relapse prevention plan (van der Zweerde et al., 2020). See Supplementary material for a more detailed description of the intervention. Patients fill out a sleep diary during the entire treatment period. The treatment takes 5–8 weeks to complete, and is offered online using text and videos. I-Sleep includes experience-based case vignettes of patients. We use an adapted mental health care version of i-Sleep in which case vignettes represent patients with comorbid psychiatric symptoms. Reading the session text and carrying out the homework exercises of i-Sleep take approximately 10–30 min daily. After every session the therapist provides online feedback, guides sleep restriction therapy and bedtimes, and motivates patients to persevere in treatment. Patients can also send questions to their therapist. In general, guidance takes about 20 min per patient per session. There are three additional 30-minute video call appointments (at the start, and after 2 and 4 weeks) to provide extra explanation, enhance commitment, and prevent drop-out. In this study the main researcher will provide the feedback ([name]). She is trained by a psychologist with extensive experience in CBT-I and i-Sleep ([name]) and under weekly supervision by [name] and another experienced CBT(-I) psychologist. I-Sleep will be delivered through the secure web-based platform the Nederlands Slaap Register (www.slaapregister.nl).

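### Section 2.6 says the self-report questionnaires remain blinded, but the patients who rate them know their arm, so every secondary outcome group except EEG is assessed unblinded

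*Protocol article*

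**What the plan says.** Section 2.6 (Randomization) goes through blinding role by role:

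- Therapist: "Due to the nature of the intervention, the therapist is not blind to treatment condition".
- Primary outcome: "The primary outcome measurement (BPDSI) is administered by a blinded and trained researcher".
- EEG: "EEG data is scored by a trained researcher who is blind to experimental condition".
- Everything else: "All other outcome assessments involve self-report questionnaires that remain blinded".

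The sentence after these adds, separately, that participant number and condition are re-coded before analysis.

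What the patients experience is described elsewhere. Section 2.3.1 gives the iCBT-I arm five sessions, online therapist feedback after each one, and three 30-minute video calls. Section 2.1 describes the other arm: "In the control arm, patients are on the waitlist and keep a sleep diary for 6 weeks, followed by STEPPS". Section 3.1 says of the control diary: "To prevent too much of a therapeutic effect, no feedback will be given". Controls are offered the same sleep treatment once the trial is over (sections 2.4 and 3.1). Intervention patients are asked to evaluate iCBT-I at T1 and T2 (section 2.5.5), which are also the outcome time points.

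**The concern.** Whether an outcome is blinded depends on who judges it. For a questionnaire or diary that is the patient, and the two arms differ in ways no patient could miss. The reason the article gives for the therapist not being blind, the nature of the intervention, applies equally to the patient.

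This matters because readers use a blinding statement to judge risk of bias. Insomnia severity, emotion regulation and mood are the outcomes that would support the proposed sleep mechanism, and the discussion names inclusion in clinical guidelines as the ultimate goal. A difference on these scales could arise wholly or partly from patients' expectations, and the sentence as written tells the reader that this has been guarded against. EEG, the one secondary outcome that patients do not rate, is optional (section 2.5.2.4), so it may be incomplete.

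**Working it through.** **Who rates each secondary outcome (section 2.5.2)**

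| Outcome group | Rater | Rater knows the arm? |
|---|---|---|
| Ultra-short BPD-C | patient | yes |
| ISI | patient | yes |
| Sleep diary | patient | yes |
| EEG headband | blinded scorer | no |
| DERS-SF | patient | yes |
| RMT-20 | patient | yes |
| Additional outcomes (quality of life, daytime functioning, positive mental health, life satisfaction) | patient, since section 2.6 classes everything outside BPDSI and EEG as self-report | yes |

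Six of the seven groups are patient-rated, and the document describes nothing that would keep patients from knowing their arm.

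**The plan's own figure**

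Inputs from section 2.7: d = 0.5, α = 0.05 (taken as two-sided; the article does not say), power 0.80, correlation 0.5, effect averaged over T1 and T2.

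- Variance factor for the mean of two measures: (1 + 0.5)/2 = 0.75.
- n per arm = 2 × (1.960 + 0.842)² × 0.75 / 0.5² = 47.1, rounded up to 48. The stated 48 is reproduced.

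**Illustration of what a reporting bias could do**

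The bias sizes (0.2 and 0.3 SD) are assumptions. So is the use of section 2.7's inputs, which are stated only for the BPDSI, for the self-report scales. No dropout is assumed.

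Probability of a significant result favouring iCBT-I with no true effect and a bias of b SD: Φ(b/SE − 1.96).

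- Unadjusted, matching the sample size calculation: SE = √(2 × 0.75/48) = 0.177.
- Baseline-adjusted, closer to the model in section 2.8, which omits the treatment main effect to control for baseline: factor 0.75 − 0.5² = 0.50, so SE = √(2 × 0.50/48) = 0.144. This is not the precision behind the stated 48; with factor 0.50 the same calculation needs only 32 per arm.

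| Bias b | SE 0.177 | SE 0.144 |
|---|---|---|
| 0.2 SD | Φ(−0.83) ≈ 20% | Φ(−0.57) ≈ 28% |
| 0.3 SD | Φ(−0.26) ≈ 40% | Φ(0.12) ≈ 55% |

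**The case against.** The best defence is that the neighbouring sentences are about staff. Read that way, the phrase may only mean that no unblinded staff member rates the questionnaires, and the article never says outright that patients are blinded. That makes the sentence loose wording rather than a deliberate claim. It does not rescue it: the absence of a staff rater does not make the actual rater blind, and the re-coding of data has its own sentence.

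It can also be said that the authors already rank the evidence. Section 3.1 contrasts the clinical interview with mere self-report, and concedes that the control condition "results in less attention from a professional compared to the iCBT-I condition" and that this may hinder interpretation. This stands for unequal attention. It does not cover patients rating themselves in the knowledge of their arm.

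Three stronger readings are tempting, and the document does not support them:

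- *The primary outcome is unblinded too.* BPDSI answers do come from patients who know their arm, and that deserves a sentence. But the interviewer is stated to be blind. That the article is silent on recording accidental unblinding is not a fault, because a condensed article may leave such detail to the full protocol.
- *Interviews in which the arm was revealed should be excluded in a further analysis.* Disclosure happens after randomisation and may well be more common among treated patients. Dropping those interviews would give up the randomised comparison and depart from the intention-to-treat analysis in section 2.8.
- *The self-report results will be put forward as blinded evidence.* Nothing in the article says so. The defect is the statement itself.

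**Conclusion.** The statement that the self-report questionnaires remain blinded is wrong as written. BPD-C, ISI, sleep diary, DERS-SF, RMT-20 and the additional self-reports are assessed unblinded. This rests on two things visible in the document: patients rate these outcomes themselves, and the arms are plainly distinguishable to them.

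How much bias follows cannot be estimated from the document. The ranges of 20% to 28% and 40% to 55% show only that a modest reporting bias would lift the false-positive rate well above the nominal 5%; they do not predict that such a bias will occur.

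The point is limited to secondary outcomes and their interpretation. Blinding of the BPDSI interviewer, the EEG scorer and the analysis data is not disputed. It should be corrected because the change is small and bears on what most of the secondary evidence can support.

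**What to change.** In section 2.6, replace the sentence by: *Patients are not blinded, so all self-report outcomes are assessed unblinded; blinding applies to the BPDSI interviewer, the EEG scorer and the re-coded data used for analysis.*

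In section 3.1, add unblinded self-rating, and the expectation effects that come with it, as a limitation alongside unequal attention. Note there that BPDSI answers also come from patients who know their arm, although the interviewer does not. Interpret differences on the self-report scales accordingly when results are reported.

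The cost is a few sentences and a less favourable description of blinding. Trial conduct, sample size and primary analysis do not change.
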